#### Brain MRI

T2-weighted brain MRI will be used to determine the number of new brain lesions over the entire 1-year period. The number of brain lesions will be defined as new or enlarging lesions or lesions reappearing at the site of previously healed lesions on T2-weighted MRI scans. Reading of the MRI will be performed by neuroradiologists in a single center, who will work blinded to the treatment arm. The MRI examinations will be carried out at the participating centers in keeping with the technical protocol.

### Secondary end points

Secondary end points at 12 months will be annual relapse rate; changes in disability measured by the EDSS score (0- to 10-point scale, where 0 is normal, 3 is mild disability, 6 is cane requirement, 7 is wheelchair use and 10 is death due to MS)
[47]; proportion of patients with relapses, classified as 0, 1–2 or >2 relapses; proportion of patients who will undergo angioplasty who present with restenosis within 12 months afterward; MRI activity at 12 months in angioplasty patients with or without restenosis; fatigue measured using the Modified Fatigue Impact Scale (M-FIS Questionnaire)
[48]; anxiety and depression measured using the Hospital Anxiety and Depression Scale (HADS-A/D questionnaire)
[49]; general cognitive state measured using the Montreal Cognitive Assessment (MoCA test)
[50]; memory/attention/calculus measured using the Paced Auditory Serial Addition test (PASAT)
[51]; impact of bladder incontinence measured using the Overactive Bladder Questionnaire (OABQ)
[52]; and adverse events. A secondary objective is to estimate the proportion of patients with CCSVI diagnosed by ECD and confirmed by venography.

### Sample size

The study was designed by taking into account (1) the need to include all patients who are potential candidates for the therapeutic benefit of angioplasty and (2) the need for a short enrollment period and a follow-up of 12 months. Since the two diagnostic categories (RRMS and SPMS) will have different participant sizes and responsiveness, the statistical power will be different in the two groups. Estimates of the treatment effect will be more precise in the largest subgroup of RRMS. For the patients with SPMS, the study will provide preliminary information, possibly requiring an extension of recruitment of SPMS subjects. The sample size calculation and the definition of the analysis plan will be different for the two types of patients.

#### Patients with RRMS

The sample size was estimated on the basis of the primary end point on MRI. We assume that the average total number of MRI active lesions in the control group is equal to 6 with a standard deviation of 7.6
[53]. The intention-to-treat (ITT) analysis of 423 patients, allocated into the two treatment arms according to a randomization ratio of 1:2 (141 in the control arm and 282 in the experimental arm), will allow us to detect an absolute mean reduction of 2.1 lesions with an α error of 0.05 (two-sided likelihood ratio test (LRT)) and a power of 90% (power analysis based on 5,000 simulations, assuming a negative binomial distribution). Thus, we will be able to highlight a 1-year mean reduction from 6 lesions in the control arm to 3.9 in the experimental arm, which corresponds to a relative reduction of 35%. Even in the presence of a higher level of variability, with a standard deviation of nine lesions, our study would have a power of 81%, to show as statistically significant the same difference. This sample size will also be able to show a reduction of at least 0.3 in the annualized relapse rate with a power greater than 93%, (0.6 vs. 0.9 in the control arm, α = 0.05, two-sided LRT). The sample size of 423 patients is also adequate for the evaluation of the combined clinical end point with a 92% power or higher to detect a 15% increase in the percentage of improved patients (with a 5% to 15% figure in the control arm, α=0.05, two-sided test on proportions). To obtain a sample size of 423, a total of 445 patients will be recruited (148 in the control arm and 297 in the experimental arm), to take into account a 5% dropout rate, leading to nonevaluation of the primary end point at 12 months.

#### Patients with SPMS

This combined clinical end point is being used, to the best of our knowledge, for the first time in this trial. Thus, the power of the study was calculated under various scenarios concerning different values of the 12 months percentage of improvement in either group. The main analysis concerns the probability of improvement, considering the worsened, the stable and the fluctuating conditions as failures. With an enrolment of 222 patients allocated according to a randomization ratio of 1:2 (74 in control arm and 148 in experimental arm), power is sufficient to detect, based on the ITT analysis, an absolute improvement ranging from 15% to 25% (α = 0.05, two-sided test on proportions), as shown in Table 
4. In order to obtain a sample size of 222, a total of 234 patients will be recruited (78 in the control arm and 156 in the experimental arm), taking into account a 5% of drop-out due to lack of evaluation at 12 months.

**Table 4 T4:** Power calculation for different scenarios of baseline values and deltas of the probability of improvement at 1 year in the combined clinical end point (intention-to-treat analysis)

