#### Clinical end point

We will use a combined end point obtained through the integration of five functional indicators clinically meaningful and measured with validated instrumental methods. These are related to walking
[41,42], balance
[43], manual dexterity
[44], bladder control
[45] and low-contrast visual acuity
[46]. Each patient, at 3, 6 and 12 months after randomization, will undergo a reevaluation using the whole battery of tests. On the basis of the published minimal real difference
[41-45], or the published clinically significant difference for low-contrast visual acuity
[46], each function will be classified as “improved/stable/worsened,” and the combined evaluation of the five functions will lead to the classification of the participant as improved/stable/worsened/fluctuating according to the following criteria: (1) improved patient, defined as the presence of significant improvement in one or more functions and stability in nonimproving functions; (2) worsened patient, defined as the presence of worsening in one or more functions and stability in nonworsening functions; (3) fluctuating patient, defined as concomitant presence of improvement and worsening in one or more functions; and (4) stable patient, defined as the presence of stability in all functions.

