### Data collection

The scheduling of examinations and tests is reported in Table 
5. The treating neurologist will be responsible for the overall medical management of patients, including pharmacological treatment for MS, as well as scheduled (every 3 months) and unscheduled follow-up visits. The treating neurologist will advise patients to contact the clinic at any time if new symptoms or complications occur. At each visit, the treating neurologist will record any new symptoms, any adverse events and their management and treatment decisions, including discontinuation of pharmacological treatments.

**Table 5 T5:** Scheduling of examinations and tests

**Time**	**Examinations and tests**
−45 days (maximum)	Clinical verification of eligibility, information to patient, informed consent (must take place before the ECD and blood tests), blood tests and ECD prescription
	Performance of ECD, blood tests
−15 days (maximum)	Baseline clinical visit, functional tests and MRI, planning of angioplastic surgery (real or sham)
0	Randomization and angioplasty (real or sham)
+3 months	Clinical visit and functional tests
+6 months	Clinical visit, ECD, MRI and functional tests
+9 months	Clinical visit
+12 months	Clinical visit, ECD, MRI and functional tests

All data will be securely stored in an electronic case report form (e-CRF). Data access will be protected by user name and password according to different profiles, depending on the user. In particular, centers will have access only to data relative to their own center, whereas the center responsible for informatics infrastructure of the CRO and the member of the DCC responsible for quality will have online access to the entire database to perform periodic quality checks. An electronic query system, managed by the CRO monitor, will be available, and every correction of original data will have to be approved by the member of the DCC responsible for data quality. The traceability of all data (original and corrected) entered into the system will be guaranteed. The research data will be stored for up to 7 years, in compliance with any integrity issues that may arise from any subsequent publications (Article 18, paragraph 1, of the D.l. 200 dated 6 November 2007). Following that time period, the data will be under the control of the treating neurologist.

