#### Patients with RRMS

In this group of patients, the evaluation of the treatment effect on the MRI primary end point (average number of lesions on MRI at 1 year) will be performed using a LRT, assuming a negative binomial model (α = 5%, two-sided test). This comparison will also be evaluated using a regression model, adjusting for some important factors, that is, time from diagnosis of MS disease, concomitant treatments and EDSS at baseline. A descriptive analysis will also be conducted on the components of this primary end point, considering separately the treatment effect on T1 active lesions and on new or enlarging T2 lesions. The effect of the treatment will also be assessed on the clinical end point, comparing the proportions of patients classified as “improved,” as defined in the “primary end point” section (α = 5%, two-sided test on proportions). The relapse rate (secondary end point) in the two treatment groups will be compared by means of a LRT, assuming a Poisson model (also adjusting for the same factors considered for the primary end point). The Poisson model assumptions will be assessed, and, in the event of evidence of overdispersion, alternative models that relax these assumptions will be considered (that is, mixed-effects Poisson model).

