#### Patients with SPMS

For the patients with SPMS subpopulation, the primary analysis will be carried out with a test on proportions, comparing the proportion of subjects in the two arms who will be classified as “improved” with respect to the clinical end point (α = 5%, two-sided test). A multivariate analysis based on a logistic regression model will be carried out, taking into account relevant factors, such as gender, time from MS diagnosis, concomitant treatments and EDSS at baseline. A secondary analysis of treatment effect will also be performed by comparing the distribution of each category of the combined end point in the two treatment groups. The treatment effect on each single functional parameter of the combined end point will also be assessed using the Hochberg correction for multiple testing
[54]. The MRI end point will be evaluated by comparing the mean number of lesions at 1 year, assuming a negative binomial model (α = 5%, two-sided LRT). In both samples (RRMS and SPMS), analyses will be performed on all secondary end points. Any deviation from the planned statistical methods will be properly documented in the study report.

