[47], the most widely used disability measure in clinical trials for MS, is an ambulation-centered scale that does not take into account cognitive impairment or upper-arm or bladder dysfunctions that are primary components of disability. The EDSS is an ordinal nonlinear scale whose serial upward changes of 0.5 or 1.0 points, confirmed at 3–6 months or unconfirmed, are commonly used in clinical trials. However, changes of 0.5 points are invalid, even if confirmed at 3 or 6 months, and, similarly, 1-point changes are not significantly more likely to occur for worsening than for improvement
[58]. When choosing the indicators of the functional composite end point, we took into account relevant parameters, that is, the prevalence and clinical relevance of impaired functions in MS, objective and validated measures, and global feasibility of the tests in terms of tolerance, time scales, costs and necessary skills. Also, all tests are instrumental and thus semiobjective, although prone to behavioral influences. An extensive review of the literature was carried out, and the specific skills and experience in the field of functional testing of the various members of the working group were taken into account. The choice was then made after reflection and collegial discussion.

Each participating center is accredited as a MS center by the National Health Service and employs professionals with the following skills: neurology, neuroradiology, noninvasive vascular diagnosis, vascular surgical radiology, physiotherapy and psychometric testing. The staff participating in the study are accredited for the ECD diagnosis of CCSVI, the venous angioplasty intervention and the measurement of the functional end points.

This clinical trial will provide answers with regard not only to the efficacy of venous angioplasty on the inflammatory component of MS but also about subjective symptoms and functions, such as motor impairments, sphincteral and visual deficits, fatigue, anxiety, depression and attention deficits, which are meaningful clinical outcomes. In fact, an important part of patients’ expectations, sustained and amplified by anecdotal data on improvement of quality of life reported in the Zamboni *et al*. study
[34], has to do with precisely these aspects.

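### The deciding test of the clinical primary end point uses no baseline functional score: it is valid, but a modest, attainable gain in power and protection against baseline imbalance is forgone in RRMS and SPMS

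*Protocol article*

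**What the plan says.** **End point.** Under Clinical end point, "each function will be classified as “improved/stable/worsened,” and the combined evaluation of the five functions will lead to the classification of the participant". Success is the "improved patient, defined as the presence of significant improvement in one or more functions and stability in nonimproving functions". Under Sample size, Patients with SPMS, the other three categories count as failures: "The main analysis concerns the probability of improvement, considering the worsened, the stable and the fluctuating conditions as failures".

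**Baseline data.** Table 5 (Data collection) schedules, at most 15 days before randomization, "Baseline clinical visit, functional tests and MRI".

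**Tests.** In RRMS, "The effect of the treatment will also be assessed on the clinical end point, comparing the proportions of patients classified as" improved, with a two-sided 5% test on proportions. The regression adjustment in that section is attached to the MRI comparison and to the relapse rate, not to this end point. In SPMS the primary analysis is the same kind of test. A logistic model follows, "taking into account relevant factors, such as gender, time from MS diagnosis, concomitant treatments and EDSS at baseline".

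**EDSS.** The Discussion explains why EDSS was not chosen as the clinical end point: it "is an ambulation-centered scale that does not take into account cognitive impairment or upper-arm or bladder dysfunctions".

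**Balance and entry.** Randomization is stratified by center and disease course. Table 1 requires EDSS 2 to 5.5 and asks for no impairment in any of the five tested functions.

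**The concern.** A patient counts as improved only if some function gains more than a published threshold. It is reasonable to expect the chance of this to depend on where each function starts, since a function that is nearly unimpaired has little to gain. Entry fixes only the EDSS range, so patients may differ in how many functions can improve, and neither stratification nor the deciding test accounts for that. The only severity measure named in the SPMS model is one that the protocol itself says misses two of the five functions (manual dexterity and bladder control).

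The end point carries weight. By the Discussion, significance on either primary end point suffices to declare superiority, and the clinical one prevails if the two conflict. It is the SPMS primary analysis, where Table 4 gives power of only 0.72 and 0.64 for a 15-point difference at control rates of 10% and 15%.

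**Working it through.** **1. The plan's own power.** Inputs from Sample size: 74 v 148 (SPMS), 141 v 282 (RRMS), two-sided α = 0.05, control rates 5%, 10% and 15%. The method is the two-proportion normal formula with Fleiss continuity correction, n1(eff) = n1 × [1 − (1 + 1/k)/(2·n1·d)]², with k = 2.

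Example, 10% v 25%: n1(eff) = 74 × (1 − 1.5/22.2)² = 64.3. The pooled rate is 0.20, the null SE 0.0611 and the alternative SE 0.0534. Then z = (0.15 − 1.96 × 0.0611)/0.0534 = 0.57, which gives power 0.715 (Table 4: 0.72).

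| Difference | Table 4 (5/10/15%) | Reproduced |
|---|---|---|
| 15 points | 0.84 / 0.72 / 0.64 | 0.834 / 0.715 / 0.633 |
| 20 points | 0.97 / 0.92 / 0.87 | 0.970 / 0.919 / 0.869 |
| 25 points | 0.99 / 0.98 / 0.97 | 0.997 / 0.987 / 0.971 |

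RRMS gives 0.992 / 0.961 / 0.920, against a stated 92% or higher. The stated power is right for the planned unadjusted test.

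**2. Gain from adjusting, by number of improvable functions.** The documents do not say how many patients have room to improve in each function, so this share is an assumption (30%, 50% or 70%). Further assumptions are latent correlation 0.3 between functions and 3% worsening per function. Arm rates are calibrated to the stated values. An uncorrected chi-square test is compared with a Mantel-Haenszel test stratified by the number of improvable functions, with 6,000 trials per scenario.

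| Scenario | Unadjusted (30/50/70%) | Adjusted (30/50/70%) |
|---|---|---|
| SPMS, 10% v 25% | 0.79 / 0.79 / 0.79 | 0.84 / 0.81 / 0.79 |
| SPMS, 15% v 30% | 0.72 / 0.70 / 0.70 | 0.79 / 0.74 / 0.71 |
| RRMS, 15% v 30% | 0.94 / 0.94 / 0.94 | 0.97 / 0.95 / 0.95 |

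Repeat runs agree to within about one point. At 5% v 20% in SPMS, 0.90 becomes 0.92 to 0.93 at the 30% share and hardly changes at higher shares. At a share of 85% there is no gain. Type I error is about 5% for both tests. The adjusted figures must be compared with the uncorrected column here. Setting 0.79 against Table 4's 0.64 would mix in the continuity correction and overstate the gain.

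**3. Gain from adjusting, logistic model with one baseline score.** SPMS, 15% v 30%: unadjusted power is about 0.72 to 0.73. Adjusted power is 0.72, 0.74, 0.76 and 0.79 at an odds ratio per SD of 1, 1.5, 2 and 3. Adjusting instead for an EDSS-like proxy correlated 0.3 with function gives no gain.

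**4. Gain from adjusting, five floor-limited functions.** In SPMS the gain is about 0 when every function has room (0.70 to 0.71). It is 3 to 4 points when 30% to 50% of patients are unimpaired in each function (for example 0.85 to 0.89, and 0.92 to 0.96).

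**5. In patients.** By normal approximation, going from 0.72 to 0.76 is worth [(1.96 + 0.71)/(1.96 + 0.58)]² ≈ 1.10, or about 22 of 222 patients. Going from 0.72 to 0.79 is worth about 1.18, or about 40.

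**6. Chance imbalance in SPMS.** The SE of the arm difference in mean number of improvable functions is SD × √(1/74 + 1/148) = SD × 0.142. With SD of 1.34 to 1.49 under the step 2 assumptions, a 2-SE imbalance is 0.38 to 0.42 functions. Multiplied by the slope of the probability of improvement on that number, this shifts the difference by about 2 to 4.5 points. The models in steps 3 and 4 give 1.0 to 3.4 points.

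**7. Events available for a model.** Expected improved SPMS patients:
- 5% v 20%: 74 × 0.05 + 148 × 0.20 = 33
- 10% v 25%: 7.4 + 37 = 44
- 15% v 30%: 11.1 + 44.4 = 55.5

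**The case against.** The strongest reply is that nothing is wrong. Design and analysis use the same test, its power figures reproduce, its error rate is held, and an unadjusted comparison in a randomized trial is valid. All of that stands. A reader might infer that Table 4 is too optimistic, that planned power is lost, or that the result would be biased. The documents support none of these.

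The gain rests on an input that the documents do not give. Five points or more requires roughly 30% of patients to have room in each function, or a strongly prognostic score. The article names neither the instruments' ceilings nor their thresholds. A reader might also infer that baseline function is the strongest available predictor of the end point. This is plausible but unproven here, and so is the ceiling mechanism.

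The SPMS covariate list is open (such as), so functional scores are not excluded and a later analysis plan could add them. This is true, but it reaches only the supplementary SPMS model. The article has itself named the deciding test in both subpopulations as unadjusted.

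Finally, SPMS is described as preliminary, and counting functions with room to improve needs a ceiling for each instrument. The first limits the consequence. The second is a sound reason to adjust for the scores themselves rather than for such a count.

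**Conclusion.** The point holds as an improvement in efficiency and robustness, not as an error. The deciding comparison of improved patients ignores baseline scores that are collected on the very functions whose change defines the end point. RRMS has no stated adjusted analysis of it, and the severity covariate named for SPMS is one that the protocol itself finds incomplete.

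The forgone gain is about 0 to 7 power points in SPMS and 0 to 4 in RRMS. The upper end applies only if many patients have little room in most functions, and the gain is near zero if most can improve in most. In SPMS a 2-SE baseline imbalance would move the estimated difference by about 1 to 4.5 points. Such an imbalance is uncommon and already covered by the test's error rate, but it would be awkward to interpret without a planned adjusted estimate. The ranges rest on the simulation assumptions above. The unadjusted analysis remains valid throughout.

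**What to change.** In Statistical analyses, for both RRMS and SPMS:

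- Pre-specify, before the code is opened, a logistic comparison of improved v not improved that includes treatment and the baseline functional scores, reported as a standardised risk difference with its confidence interval.
- In SPMS, where about 33 to 55 events are expected, one summary of the five scores defined in advance may be preferable to five separate terms.
- Name the functional scores in the SPMS covariate list, and give RRMS the same analysis.
- Keep the unadjusted test on proportions, which sized the SPMS sample, reported alongside. State in advance which of the two carries the 5% test. The power gain is realised only if the adjusted one does, while the interpretive protection comes either way.

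The cost is wording, slightly more analysis work and a modest number of covariates for the SPMS events. No new data, visits or patients are needed.

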	**Probability of improvement at 1 year in the control group**		
**Delta of improvement in the experimental group**	**5%**	**10%**	**15%**
15%	0.84	0.72	0.64
20%	0.97	0.92	0.87
25%	0.99	0.98	0.97

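### SPMS power is called sufficient for a 15-point improvement, but Table 4 supports that only near a 5% control rate

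*Protocol article*

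**What the plan says.** All references are to the protocol article.

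- **Sample size, Patients with SPMS.** The design is "With an enrolment of 222 patients allocated according to a randomization ratio of 1:2 (74 in control arm and 148 in experimental arm"). For this sample the text states that "power is sufficient to detect, based on the ITT analysis, an absolute improvement ranging from 15% to 25" per cent, with the test given as "α = 0.05, two-sided test on proportions), as shown in Table" 4. The same paragraph says the combined clinical end point is new, and that power was therefore worked out under several scenarios.
- **Table 4.** The columns are headed "Probability of improvement at 1 year in the control group" and run over 5%, 10% and 15%. The row for a 15-point increase reads "15% 0.84 0.72 0.64". The row for 20 points reads "0.97 0.92 0.87". The row for 25 points gives 0.99, 0.98 and 0.97.
- **Sample size, opening paragraph.** "For the patients with SPMS, the study will provide preliminary information, possibly requiring an extension of recruitment of SPMS subjects".
- **Sample size, Patients with RRMS.** The RRMS sample is called adequate for the same clinical end point, the same 15-point increase and the same 5% to 15% control range, with power of 92% or higher.
- **Statistical analyses, Patients with SPMS.** The primary SPMS analysis is a two-sided 5% test comparing the proportions improved.

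**The concern.** The summary sentence makes an unconditional claim and cites a table that does not bear it out. In two of the three scenarios at 15 points, the table gives power well under the usual 80%, and further below the 90% to 92% that the article works with for RRMS.

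The control rate decides whether the claim holds, and it is not known in advance: the article says this end point has not been used before. The SPMS comparison is the primary test in its own subgroup. If it is null, the power statement is what a reader would turn to when asking which effects have been ruled out. Taken at face value, it suggests that a 15-point benefit would have been found. On the article's own figures, that benefit would be missed with probability 1 − 0.72 = 28% at a 10% control rate and 1 − 0.64 = 36% at 15%.

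**Working it through.** **Inputs.** From Sample size, Patients with SPMS: n₁ = 74 control, n₂ = 148 experimental, two-sided α = 0.05. From Table 4: control rates p₁ of 5%, 10% and 15%, and increases of 15, 20 and 25 points.

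**Formula.** The article does not say which version of the test on proportions was used. A pooled-variance z-test with continuity correction matches the table:

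power = Φ{[(p₂ − p₁) − c − 1.96·SE₀] / SE₁}, where

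- c = ½(1/74 + 1/148) = 0.0101
- SE₀ = √[p̄(1 − p̄)(1/74 + 1/148)], with p̄ the pooled proportion
- SE₁ = √[p₁(1 − p₁)/74 + p₂(1 − p₂)/148]

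**One cell in full (10% against 25%).** p̄ = (74·0.10 + 148·0.25)/222 = 0.20; SE₀ = 0.0570; SE₁ = 0.0498. Then (0.15 − 0.0101 − 1.96·0.0570)/0.0498 ≈ 0.567, and Φ(0.567) = 0.715. Table 4 prints 0.72.

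**All nine cells (calculated, with the printed value in brackets).**

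| Increase | Control 5% | Control 10% | Control 15% |
|---|---|---|---|
| 15 points | 0.834 (0.84) | 0.715 (0.72) | 0.633 (0.64) |
| 20 points | 0.970 (0.97) | 0.919 (0.92) | 0.869 (0.87) |
| 25 points | 0.997 (0.99) | 0.987 (0.98) | 0.971 (0.97) |

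Every cell agrees within 0.01. The same formula for RRMS (141 against 282, 15% against 30%) gives 0.920, in line with the 92% stated there. The inflation for dropout also holds: 222/0.95 = 233.7, hence 234.

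**Does the choice of test change the picture at 15 points?**

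| Test | Control 10% | Control 15% |
|---|---|---|
| Pooled z, continuity-corrected | 0.715 | 0.633 |
| Pooled z, uncorrected | 0.779 | 0.699 |
| Chi-square, exact power | 0.794 | 0.706 |
| Fisher exact | 0.774 | 0.686 |
| Unpooled z | 0.853 | 0.763 |

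Only the unpooled z-test, which is liberal here and does not match Table 4, passes 0.80 at a 10% control rate. None passes at 15%.

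**Smallest increase with 80% power, 74 against 148.** Solving the continuity-corrected formula for p₂ − p₁ gives 14.3, 16.6 and 18.2 points at control rates of 5%, 10% and 15%. Without the correction the figures are about 13.0, 15.4 and 17.1. Held at 15 points, the corrected formula reaches 80% only for control rates up to about 6%.

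**The case against.** The strongest reply is that nothing is hidden. The sentence sends the reader to Table 4, which follows directly and prints the low figures. The article sets no numerical threshold for sufficient power; 80% is convention. Seven of the nine cells pass it, and the sentence can be read loosely as a range of detectable effects that depends on the control rate. The opening paragraph of Sample size says power will differ between the two disease courses and calls the SPMS information preliminary. The Study reports section adds a check of the sample size assumptions on patients with one year of follow-up.

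Most of this stands, and it limits the weight of the point. It does not remove it. The sentence names 15 points without condition, and the article itself attaches the word adequate to 92% or higher for the same end point, increase and control range in RRMS. Nowhere else does it offer 0.64 or 0.72 as enough. The caveat about preliminary information sits apart from the power claim and is not tied to it.

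Three stronger readings are tempting but not supported:

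- **That the power calculation is wrong.** It is not; Table 4 reproduces.
- **That the 5% control rate is unrealistically low because chance variation in five functions would itself produce improved patients.** The article gives no error rates for the tests, so this would rest on assumed figures, and low assumed rates are compatible with 5%.
- **That the SPMS test should give way to estimation only.** That is a design change which a loose summary sentence does not call for.

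**Conclusion.** The point holds as a misstatement in the power summary, not as an error in the calculation or a failure of the design. Table 4 supports sufficient power at every control rate considered only for increases of 20 to 25 points (0.87 or more). For 15 points the power is 0.84, 0.72 and 0.64, so the claim is met only near a 5% control rate.

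This rests on the article's own sample, test level and table. The one outside element is the 80% benchmark; against the 90% to 92% used for RRMS, even the 0.84 cell falls short. The detectable increases of about 14, 17 and 18 points also assume the continuity-corrected test, which is inferred from its match to Table 4. Without the correction they fall by a little over one point each, and the conclusion is the same.

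The point is worth correcting because it bears on how a null SPMS result is read. It changes no sample size, analysis or decision rule.

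**What to change.** Replace the summary sentence under Patients with SPMS with wording such as: power is at least 0.87 for an absolute increase of 20% to 25%; for 15% it is 0.64 to 0.84 depending on the control rate, and the smallest increase detectable with 80% power is about 14, 17 and 18 points at control rates of 5%, 10% and 15%.

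Add a reference to the statement in the opening paragraph of Sample size that SPMS results are preliminary, and say that a null SPMS result would not exclude a 15-point benefit. Naming the continuity-corrected test in the note to Table 4 would let a reader check the figures.

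Keep the two-sided 5% SPMS test and the planned 222 evaluable patients. The cost is a sentence or two and a less favourable stated figure, with no extra patients.
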